### Recruitment

Health talks on e-health, brisk walking, and cognitive frailty will be conducted in community centres for older people. At the end of the talks, participants will be directly recruited. The programme will be introduced to our collaborative organizations. We will produce both printed and electronic promotional materials (e.g. posters, and short videos). With the help of the collaborative organizations, the promotional materials will reach the members of the collaborative organizations through the webpage of the hosting and collaborative organizations, post, email, WhatsApp, and social media (e.g. Facebook, YouTube Channel). The project team and the staff members of the collaborative organizations will help recruit potentially eligible participants. To enhance the recruitment rate, a cognitive frailty symptom checklist and the eligibility criteria will be posted in all the promotional materials. We will announce to all the potential participants and the staff member of the collaborative organizations to read the information and validate if the potential participants fulfil the eligibility criteria before eligibility screening will be conducted on them. This is to ensure that the interested participants are more likely to be eligible to join this study. With these measures, the estimated recruitment rate is expected to be above 50%.

### Assignment of interventions

All participants will be individually randomized into groups. Permuted block randomization will be used to randomly select block sizes and a group ratio of 1:1 will be used. A random allocation sequence list will be generated by the web-based application Research Randomizer [57]. The process will be conducted by an independent statistician, who will not participate in any other parts of the proposed study. The statistician will assign group labels to the participants based on their sequence of entries referring to the random sequence list, thus ensuring that other members of the research team cannot foresee the group allocations [58].

In the proposed study, only the outcome assessor will be blinded to the group labels, as it will be impossible to blind the participants and interventionists. The group labels will not be revealed to the outcome assessor and will not appear on any documents. The participants, family members and staff of the centres will be prohibited from disclosing the group labels of the participants. It will not be possible to blind the participants or the interventionists. To further minimize the risk of contamination in the same centre, the participants will be instructed to not teach the intervention-related e-health skills (e.g. the self-paced brisk walking training function in Samsung Health) to the participants in the control group. The WhatsApp groups will only be managed by the interventionists, who will forbid non-participants from joining.

All data saved on Qualtrics are coded so that no personal identifiers will be saved on Qualtrics. A code will be assigned to a participant. A codebook keeps the participants’ names and phone numbers. Phone numbers and names are marked on the codebook because we want to make sure that participants with the same name can be identified. The data collector assigns a code to each participant when they are being recruited. The data collector does not participate in data analysis or any other parts of the study. The codebook is saved on a cloud server (i.e. OneDrive, TWC) which is only accessible to the PI. Data will be collected using an online data collection platform (i.e. Qualtrics). In the online data set, only the code is saved, and the data set contains no identifiers. Only the PI have the access to both the codebook on OneDrive TWC and the dataset on Qualtrics. There are no direct links between the code and the participants’ identifiers. Codebook with personal identifiers (i.e. name and telephone number) will be deleted upon the completion of the study.

### Statistical methods

Demographic and outcome data at baseline will be reported either as means with standard deviation or as frequencies with percentages based on their level of measurement. Generalized estimating equations (GEE) will be used to separately test the hypotheses on the five outcomes, which are the dependent variables (i.e. MVPA, cognitive frailty, cognitive function, physical function, and physical activity motivation). The independent variables will be the same across all GEEs: group (two categories: intervention and control groups), timepoint (three categories: T0, T1, T2), and group x timepoint. The primary interpretation of the results will be based on the analysis based on the intention-to-treat principle without adjusting for possible covariates [60, 61]. Sensitivity analyses will be conducted and reported to compare the results of different methods of analysis, such as intention-to-treat and per-protocol analyses [62]. The level of significance will be set at 0.05. Missing data will be managed following Jakobsen’s algorithm according to the missing pattern with various methods (e.g. no imputation, multiple imputations) [63].

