### Outcomes

Demographic data include age, gender, level of education, number of chronic illnesses, financial satisfaction, living arrangement, years of smartphone usage, and perceived ability to use a smartphone. Demographic data will be collected at T0 (i.e. week 0) only. The primary outcome is MVPA. The four secondary outcomes are cognitive frailty, cognitive function, physical function, and physical activity motivation. All outcome data will be collected at T0 (i.e. week 0), T1 (i.e. week 15), and T2 (i.e. week 41).

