#### MVPA (primary outcome)

MVPA will be quantified in MVPA minutes measured by a wrist-worn ActiGraph GT3X + , which has good criterion validity in differentiating between MVPA and non-MVPA in older people compared with indirect calorimetry (sens = 0.836, spec = 0.894, AUC = 0.932, *p*< 0.001) [45]. An MVPA minute is defined as a minute in which the ActiGraph mounted on the right wrist records physical movement (i.e. vector magnitude) of above 4212.9 count/min [45]. Only at least 10 min of continuous MVPA will be counted as valid MVPA minutes because the World Health Organization advises that engaging in MVPA for 150 min per week has health benefits when each session lasts for > 10 min [17]. Physical activity will be quantified by valid MVPA minutes measured over 7 consecutive days, as a 7-day interval is sufficient to discern an individual’s pattern of physical activity and is a widely used standard in studies of physical activity [46]. Only MVPA minutes measured on valid days (i.e. ActiGraph wearing time > 10 h/day) for a valid period (i.e. valid days > 3) will be considered valid [47].

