### Participant timeline

As shown in Table 2 and Fig. 1, potential participants will be enrolled on the study in the phase of enrolment. The potential participants will be screened for eligibility. Eligible participants will be invited to sign the written informed consent after being explained the study details. After the enrolment phase, the pre-treatment assessment (T0, i.e. week 0) will commence. Demographic and outcome data will be collected. After that, participants will be randomly allocated to either the intervention or control group. Then, the interventions will commence. In the week immediately after the intervention (T1, i.e. week 15), the post-treatment assessment will commence and outcome data will be collected. Data of all outcome variables will be collected once again in the 6-month (i.e. 26 weeks) follow-up period (T2, i.e. week 41).

**Table 2 Tab2:** Schedule of enrolment, intervention, and assessments (SPIRIT-Figure)

Timepoint	Enrolment	Pre-treatment assessment	Allocation	Intervention	Post-treatment assessment	6-month follow-up
		T0			T1	T2
Enrolment						
Eligibility screen	x					
Informed consent	x					
Group allocation			x			
Interventions						
E-health				x		
CBCI				x		
Data collection						
Demographic		x				
Outcome						
MVPA		x			x	x
Cognitive frailty		x			x	x
Cognitive function		x			x	x
Physical function		x			x	x
Physical activity motivation		x			x	x

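### The primary GEE treats pre-randomisation MVPA as an outcome and makes the unadjusted analysis primary, giving up whatever precision adjustment for baseline MVPA would bring

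*Protocol article*

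**What the plan says.** Under Statistical methods, the article states: "Generalized estimating equations (GEE) will be used to separately test the hypotheses on the five outcomes, which are the dependent variables". The independent variables are the same in each model: "group (two categories: intervention and control groups"), then "timepoint (three categories: T0, T1, T2), and group x timepoint". The primary interpretation is "based on the intention-to-treat principle without adjusting for possible covariates". Sensitivity analyses are left open, with intention-to-treat and per-protocol given as examples. No baseline-adjusted analysis is named.

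The primary outcome is continuous: "MVPA will be quantified in MVPA minutes measured by a wrist-worn ActiGraph GT3X" (MVPA section). On timing, the Outcomes section says "All outcome data will be collected at T0 (i.e. week 0), T1 (i.e. week 15), and T2 (i.e. week 41"), and the Participant timeline, after describing the T0 assessment, continues: "After that, participants will be randomly allocated to either the intervention or control group".

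The sample size section also counts three repeated measures including T0. It gives no numerical effect size, SD or within-person correlation.

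**The concern.** Because T0 precedes allocation, the groups can differ at T0 only by chance. The model nevertheless spends a parameter on that difference. Its interaction terms subtract the observed T0 difference in full, whatever the strength of the relation between baseline and follow-up MVPA. A baseline-adjusted contrast subtracts only the part that predicts follow-up.

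What is at stake is the width of the confidence interval for the primary contrast. The trial is described as non-inferiority, a design in which the confidence limit decides the conclusion, so avoidable width matters. The same model form is also set for the secondary outcomes. This is a choice that the article makes explicitly, not a detail left to a later analysis plan.

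**Working it through.** **Inputs.** From the article: the model terms, the unadjusted primary interpretation, T0 before randomisation, three timepoints, 1:1 allocation, power 0.90, significance level 0.05 (sidedness not stated; two-sided assumed here), 132 before the dropout allowance. Not in the article, so assumed over a range: rho (correlation between T0 and a follow-up visit) and k = SD0/SD1. The 132 cannot be reproduced without an effect size, SD and correlation.

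**Step 1: what the interaction terms estimate.** Group, three-level time and their product give six parameters for six group-by-time means. With an identity link and complete data, the group × T1 coefficient is therefore (difference in means at T1) − (difference in means at T0). A simulated trial with 66 per arm and rho 0.5 confirms it. The GEE coefficient was 0.35558 under both independence and exchangeable working correlation, equal to the raw difference in mean change. Its standard error was 0.145, against 0.122 for analysis of covariance (ANCOVA) on the same data. With dropout the identity is only approximate.

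**Step 2: large-sample variances**, in units of SD1², with the common factor 2/n per arm left out.
- Change from T0: k² + 1 − 2·rho·k
- Adjusted for T0: 1 − rho²
- Difference: (k − rho)², which is never negative and is zero when k = rho, that is SD0 = rho × SD1

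**Step 3: ratio adjusted/change = (1 − rho²)/(k² + 1 − 2·rho·k).**

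| k | rho 0.3 | rho 0.5 | rho 0.7 |
|---|---|---|---|
| 1.0 | 0.91/1.40 = 0.65 | 0.75/1.00 = 0.75 | 0.51/0.60 = 0.85 |
| 0.7 | 0.91/1.07 = 0.85 | 0.75/0.79 = 0.95 | 0.51/0.51 = 1.00 |
| 0.5 | 0.91/0.95 = 0.96 | 0.75/0.75 = 1.00 | 0.51/0.55 = 0.93 |

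At k = 1, 2,000 simulated trials per value of rho gave ratios of 0.63, 0.77 and 0.83.

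**Step 4: illustration on the power scale.** Suppose 132 gives a single change-score contrast exactly 90% power, two-sided 0.05. Power after adjustment is Φ(3.2415/√ratio − 1.96). At k = 1 this is 98.0%, 96.3% and 94.0% for rho 0.3, 0.5 and 0.7. At k = 0.7 it is 94.0%, 91.4% and 90.0%.

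**Step 5: does dropping the group main effect do the same job?** Keep three timepoints but let group enter only through group × T1 and group × T2.
- Independence working correlation: the T1 contrast becomes the raw T1 difference, with no baseline adjustment. Its variance relative to the planned contrast is 1/(k² + 1 − 2·rho·k). At rho 0.7 this is 1/0.60 = 1.67 (k = 1), 1/0.51 = 1.96 (k = 0.7) and 1/0.55 = 1.82 (k = 0.5).
- Exchangeable, taking the same rho between all visits and the same SD at T1 and T2: the baseline slope is set to the pooled working correlation a = (2·rho·k + rho)/(k² + 2), and the variance is 1 + a²k² − 2a·rho·k. At k = 1 this matches ANCOVA. At k = 0.7, rho 0.7, a = 1.68/2.49 = 0.675 and the variance is 0.562, so the ratio to the planned contrast is 0.562/0.51 = 1.10. At k = 0.5, rho 0.7, a = 1.40/2.25 = 0.622 and the ratio is 0.661/0.55 = 1.20.

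Simulation with 66 per arm gave the same picture: about 1.6 to 2.0 under independence at rho 0.7, and about 1.1 to 1.2 under exchangeable at rho 0.7 with k below 1.

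**The case against.** The strongest reply is that nothing here is invalid. The planned contrast is an unbiased randomised comparison, and choosing between two valid estimators can look like taste. It is true that no bias is involved. But the T0 values are already collected, and adjustment has essentially no cost in precision even where it gains nothing, so more than taste is involved.

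Second, the gain may be small. Entry requires under 150 minutes of MVPA per week, and both arms are trained towards more activity, so T0 values may well be less spread than follow-up values. This stands: a reader might infer that the planned contrast always has larger variance, or that 15–35% is lost, but the first fails when SD0 = rho × SD1 and the second assumes equal SDs. Likewise, subtracting the whole T0 difference over-corrects only when the slope of follow-up on baseline is below 1; with SD0 < rho × SD1 it under-corrects.

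Third, a reader might infer that the stated power is too high. The documents do not support that. The power calculation also included T0 as a repeated measure, and its inputs are not given.

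Fourth, covariates are excluded only from the primary interpretation. An adjusted sensitivity analysis is not forbidden, though none is named, and it would not govern the primary conclusion.

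Finally, the algebra applies to continuous outcomes with an identity link. The article states no link, and cognitive frailty is a six-level ordered variable, so the argument does not carry over to it directly.

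**Conclusion.** The point holds as one of efficiency. The primary model gives an unbiased contrast that, in large samples, is never more precise than a baseline-adjusted one and is less precise unless SD0 = rho × SD1. The size cannot be fixed from the documents. It runs from about 35% of the variance (equal SDs, rho 0.3) to nothing (for example SD0/SD1 = 0.7, rho 0.7). These figures assume complete data and an identity link; with dropout they are approximate. There is no evidence here of bias, of an invalid test, or of an error in the stated 90% power.

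**What to change.** Make the primary model a GEE with T1 and T2 MVPA as outcomes and group, timepoint, group × timepoint, T0 MVPA and T0 MVPA × timepoint as terms. The last term lets each visit have its own baseline slope. Use the same form for the continuous secondary outcomes, each with its own baseline. Keep the planned unadjusted three-timepoint GEE as a sensitivity analysis.

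Do not just remove the group main effect from the three-timepoint model. The article names no working correlation, and under independence or exchangeable that version can widen the interval.

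The cost is a change of analysis wording; no new data are needed. The plan should also say how a participant without a valid T0 ActiGraph period is handled, since T0 becomes a covariate. The multiple imputation already mentioned under Statistical methods could serve.

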### Ethics and dissemination

All participants will be required to sign the written informed consent to participate in the proposed study. The consent will be obtained by the research assistant after explaining the study to the participants according to the information materials. No identifying images or other personal or clinical details of participants are presented here or will be presented in reports of the trial results. The participant information materials and informed consent form are available from the corresponding author on request.

In case there are changes in the protocol, the research team will notify the sponsor, funder, and Research Ethics Committee. Then, the research venues (i.e. centres for older people) will be informed and a copy of the revised protocol will be sent to them. If there are any deviations from the protocol, the changes will be fully documented using a breach report form and the details in the clinical trial registry will also be updated.

After the completion of the study, only the research team members have the right to access the final full dataset.

The findings will be disseminated in peer-reviewed journals and presented at international and local conferences with themes related to this area. The research team complies with the authorship eligibility guideline recommended by the International Committee of Medical Journal Editors [64].

Details of the protocol, participant-level data, and statistical codes are available from the corresponding author on request.

## Discussion

Older people with cognitive frailty are potentially treatable to prevent further adverse health outcomes, the policymakers should put cognitive frailty, this relatively new health marker, a priority to treat in primary healthcare settings. E-health through smartphones is innovative which has great potential in developing effective interventions to promote health behaviours (e.g. physical activity) in older people with cognitive frailty and other health concerns (e.g. dementia) [44, 65]. This e-health brisk walking intervention may provide effective interventions to promote cognitive health prevention and preservation in primary healthcare settings. This project is innovative in fostering collaboration between academic and community settings (e.g. elderly community centres) where used to provide social and recreational activities, to provide potentially effective primary health promotion services. The project will launch an e-health intervention in several community centres for older people. Although there will only be approximately 192 participants in the study, we will continue to promote the adoption of the intervention in different community centres during and after the completion of the proposed study. A training package with written and video materials will be produced to facilitate the adoption of the intervention by other unparticipated elderly community centres. If the intervention proves effective in reducing cognitive frailty, the health of older people is expected to improve as well. Older people will benefit from living more independent lives, having fewer chronic diseases (e.g. dementia) and having better functionality (e.g. better mobility).

### Trial status

Recruitment is expected to begin on the 1st of May 2023 and until the 31st of July 2024.

## Data Availability

The data will be provided upon request.

## Abbreviations

MCI: Mild cognitive impairment
MVPA: Moderate-to-vigorous physical activity
BCT: Behavioural change technique
RAPA: Rapid Assessment of Physical Activity
GDS: Geriatric Depression Scale
MoCA: Montreal Cognitive Assessment
PAR-Q: Physical Activity Readiness Questionnaire
RMPAM: Revised Motivation for Physical Activity Measure
GEE: Generalized estimating equations
